### Power Calculation

The power calculation is based on the primary outcome. We used the most representative clinical study we could identify and attempted to modify to the current setting. An 8-week RCT using risperidone plus memantine in stable schizophrenia patients (*N* = 40) reported a reduction in PANSS negative of −2.8 (SD 1.6) with memantine compared to −0.8 (SD 0.9) with placebo (79). Assuming a similar response, we expect add-on memantine to induce −2 ± 2 point more reduction in PANSS negative compared to amisulpride monotherapy. An *a priori* Student *t*-test (two-sided) with significance level α of 0.05 and a desired power (1-α) of 80%, shows that 16 completed patients in each arm is needed.

To increase power of secondary analyses, enrollment will continue until 18 participants in each arm have completed examinations. Moreover, AMEND will be extended to 12 weeks based on the median trial duration in the meta-analysis of add-on memantine [12 weeks (mean 11.5 weeks)] (42). Based on our center’s 20 years of experience with recruitment and treatment of antipsychotic-naïve patients, we expect an inclusion rate of 2 patients per month and an attrition rate of 25%. Thus, recruitment of 46 patients will take approximately 2 years.

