**Materials and Equipment:**

Antipsychotic-naïve patients with first-episode psychosis will be randomized to 12 weeks treatment with [amisulpride + memantine] or [amisulpride + placebo]. We aim for a minimum of 18 patients in each treatment arm to complete the trial. Brain mapping will be performed before and after 12 weeks focusing on glutamate and neuromelanin in predefined regions. Regional glutamate levels will be probed with proton magnetic resonance spectroscopy (MRS), while neuromelanin signal will be mapped with neuromelanin-sensitive magnetic resonance imaging (MRI). We will also perform structural and diffusion weighted, whole-brain MRI. MRS and MRI will be performed at an ultra-high field strength (7 Tesla). Alongside, participants undergo clinical and neuropsychological assessments. Twenty matched healthy controls will undergo similar baseline- and 12-week examinations, but without receiving treatment.

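### Two figures in the power calculation do not follow from their inputs: the named t-test needs 17 completers per arm, not 16, and 36 completers at 25% attrition need 48 recruits, not 46

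*Protocol article*

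**What the plan says.** All the relevant statements but one are in the Power Calculation section of the protocol article.

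- **Planning effect.** The section cites an 8-week trial of add-on memantine with PANSS negative changes of −2.8 (SD 1.6) and −0.8 (SD 0.9), and says this source was adapted to the present trial. It then writes "we expect add-on memantine to induce −2 ± 2 point more reduction in PANSS negative compared to amisulpride monotherapy".
- **Test and error rates.** "An *a priori* Student *t*-test (two-sided) with significance level α of 0.05" and "a desired power (1-α) of 80" per cent. The label on the power is evidently a slip for 1−β and does not affect the calculation.
- **Required number.** The section concludes that the calculation "shows that 16 completed patients in each arm is needed".
- **Operative target.** To strengthen the secondary analyses, enrolment goes on until 18 per arm have finished. The abstract (Materials and Equipment) agrees: "We aim for a minimum of 18 patients in each treatment arm to complete the trial".
- **Recruitment forecast.** The section expects 2 inclusions per month and "an attrition rate of 25%. Thus, recruitment of 46 patients will take approximately 2 years".

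**The concern.** The section names a specific test and gives every input that the test needs, so a reader can recompute the required number, and the result is not the printed 16. The recruitment figure is introduced as a consequence of the attrition rate, yet that rate applied to 46 falls short of the 36 completers set a few lines earlier.

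What is at stake is whether the reported sample-size justification is accurate. It is likely to be repeated when the results are reported. As printed, it credits 16 per arm with a power that the named test does not reach, and it sets a recruitment forecast that on average misses the trial's own completion target.

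**Working it through.** **Inputs** (Power Calculation, except allocation): difference δ = 2; common within-arm SD σ = 2, reading the ± 2 as the SD; two-sided α = 0.05; power 80%; 1:1 allocation (Randomization section); attrition 25%; 2 inclusions per month; target 18 completers per arm, 36 in all.

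**Step 1. Reproduce the stated 16.** Normal approximation for two means:

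n per arm = 2 (z₀.₉₇₅ + z₀.₈₀)² (σ/δ)² = 2 × (1.960 + 0.842)² × 1 = 15.70, rounded up to 16.

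This matches the printed figure, so the reading of ± 2 as the SD is very probably the intended one. A one-sided t-test would need 14, so the two-sided reading also fits.

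**Step 2. Apply the test that the section names.** For a two-sided t-test with n per arm, power comes from the noncentral t distribution with 2n − 2 degrees of freedom and noncentrality δ / (σ√(2/n)), which is √(n/2) here because δ = σ.

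| n per arm | df | noncentrality | power |
|---|---|---|---|
| 16 | 30 | 2.83 | 78.1% |
| 17 | 32 | 2.92 | 80.7% |
| 18 | 34 | 3.00 | 83.0% |

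The smallest n with at least 80% power is 17. At 16 the shortfall is 80 − 78.1 = 1.9 percentage points.

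**Step 3. Apply the attrition rate.**

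- Expected completers from 46 recruits: 46 × (1 − 0.25) = 34.5, or 17.25 per arm.
- Recruits needed for 36 completers: 36 / 0.75 = 48.
- Attrition at which 46 recruits would give 36 completers: 1 − 36/46 = 21.7%.
- Completion target that 46 would serve at 25% attrition: 34 / 0.75 = 45.3, rounded up to 46, that is 17 per arm. The section states neither 21.7% attrition nor a target of 34.

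**Step 4. Time and power under each recruitment figure.**

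- 46 recruits at 2 per month take 23 months; 48 take 24 months. Both are about 2 years.
- With 34 completers (17 + 17), power is 80.7%; with 35 (17 + 18), it is 81.9%. Both are above 80%.

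**Step 5. Compare the SD with the source.** The source trial's pooled within-arm SD is √((1.6² + 0.9²)/2) = 1.30. The same t-test would need 8 per arm at that SD, so the planning value of 2 raises the sample size.

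**The case against.** The strongest reply is that nothing in the conduct of the trial depends on either figure. Sixteen is a standard approximation and is one patient per arm from the exact answer. The trial is not planned to stop at 16: the target is 18 per arm, with 83.0% power. The figure of 46 belongs to a timeline sentence, and enrolment is governed by completions. All of this stands, and it limits the consequence. It does not make the figures correct: the section names the Student t-test and not an approximation, and it presents 46 as following from the stated rates.

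Two stronger readings are tempting, and the document does not support them.

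- *The trial will fall short of 18 per arm.* A reader might infer this from 34.5 expected completers. It would require enrolment to stop at 46, and the section says that enrolment continues until 18 per arm have completed.
- *The SD of 2 is wrong because it is not the source trial's SD.* A reader might infer this from the assumption of a similar response next to SDs of 1.6 and 0.9. But the section says that the source was adapted, states no derivation of the 2 that could fail to reproduce, and chooses a value larger than the pooled 1.30. What is missing is a reason for the choice, which a condensed article may leave to the full protocol. The document also gives no SD for antipsychotic-naïve first-episode patients, so power figures at larger SDs would rest on assumption alone and are no evidence of an error here.

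**Conclusion.** Both figures are wrong as written, and both errors are small. The named test needs 17 completers per arm; 16 gives 78.1% power. At 25% attrition, 36 completers need 48 recruits; 46 give an expected 34.5. The errors amount to one patient per arm in the required number, and two recruits or one month in the forecast.

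The planned power is not in doubt on the plan's own assumptions: 83.0% at 18 per arm. Even if recruitment did end at 46, the expected 34 to 35 completers would give about 81%.

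The conclusion assumes that ± 2 is the common within-arm SD, that the printed power label means 1−β, that allocation among completers is equal or differs by one, and that 25% attrition applies to all recruited patients. It makes no claim about whether SD 2 is the right planning value.

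**What to change.** Restate the Power Calculation paragraph:

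1. Give 17 completers per arm as the number the two-sided t-test needs at difference 2 and SD 2, and say that the planned 18 per arm gives 83% power on those assumptions. Correct the power label to 1−β.
2. Either forecast 48 recruits for 36 completers (24 months at 2 per month, still about 2 years), or keep 46 and state that it is expected to yield 34 to 35 completers with about 81% power. The first option agrees with the 18-per-arm target in the abstract and leaves the completion rule untouched.

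The cost is the rewording of one paragraph. No new data are needed, and neither the design nor the analysis changes. The required number rises by one per arm, and under the first option the forecast lengthens by one month.

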## Discussion

By rational combination of two licensed, off-patent drugs, amisulpride and memantine, AMEND aims to optimize treatment of psychosis, especially the accompanying negative and cognitive symptoms, alongside with unraveling the signature of memantine response. If successful, AMEND will provide pivotal neurobiological evidence for future stratification of patients with first-episode psychosis before initial antipsychotic treatment.

There are few potential risks related to participating in the AMEND study. Side effects of memantine are relatively mild compared to antipsychotic medication. In previous memantine add-on RCTs in schizophrenia patients, the reported side effects did not differ from placebo (42) and chronic patients treated with memantine as add-on treatment had an improvement compared to placebo (79), why we assume that the added treatment also will improve patients with first-episode psychosis. The participants will have the advantages of a thorough examination program with more detailed psychopathological and neuropsychological testing than normally provided.

Magnetic resonance imaging procedures have not been associated with any health risk, however, the examination might cause discomfort for people with claustrophobia and anxiety. Participants will be followed carefully during the project and any potential discomfort will be attempted minimized by research staff. Great care will be taken by the research group to ensure that all examinations are carried out as smoothly and efficiently as possible, including breaks when needed. Scanning will be discontinued in cases of discomfort or anxiety, and communication between staff and participants will be possible during the whole scan.

Participants with head/neck tattoos or permanent make-up might experience warming and soreness of the painted area, and scanning will be interrupted should these symptoms arise. Incidental findings on MRI scans might lead to worrying and further clinical work-up. Blood samplings might cause discomfort for some people but will be taken by trained personal and under hygienic circumstances.

Participants can withdraw from the study at any time without explanation, and without any consequences for the following treatment.

Regarding the statistics, our power calculation and number of participants are not sized for all exploratory analyses, but our RCT design and previous pilot data, justify the rationale for conducting these tests. Admittedly, a mean 2-point reduction in PANSS negative symptoms may only represent a modest clinical improvement for the individual patient participating in this study. However, the RCT design in combination with 7T MRS data will provide strong neuroscientific evidence on how NMDARs may mediate effects on unresolved symptom domains. If successful, the combined clinical and neurobiological insights from AMEND will provide an important steppingstone, which will have major impact for further research, for stakeholders in the pharmaceutical industry, and for future patients with psychosis.

With the ambitious goal of moving clinical psychiatry toward pre-treatment stratification based on pathophysiological markers, AMEND will provide evidence for rational drug repurposing to optimize treatment outcome for patients with psychosis.

## Ethics and Dissemination

The trial has been approved by the Danish Health and Medicines Authority, the National Committee on Health Research Ethics, Danish National Committee on Biomedical Research, and the Danish Data Protection Agency. Trial participation presupposes oral and written informed consent of all participants. Memantine will be used off-label, and tolerability and clinical symptoms will be monitored closely. Personal integrity and privacy concerning participants will be protected by the Danish Law of Health. The study will be conducted in accordance with the Helsinki Declaration II and monitored according to Good Clinical Practice principles (ICH-GCP). AMEND is registered at EudraCT nr: 2021-001061-20 and ClinicalTrials.gov (NCT04789915). The trial can be subjected to quality audit. Research data and results (positive and negative), will be presented at national and international scientific meetings and conferences. Articles will be submitted to peer-reviewed journals. Authorships will adhere to the International Committee of Medical Journal Editors statement (ICMJE).^2^

## Ethics Statement

The studies involving human participants were reviewed and approved by Danish Health and Medicines Authority, the National Committee on Health Research Ethics, Danish National Committee on Biomedical Research, and the Danish Data Protection Agency. The patients/participants provided their written informed consent to participate in this study.
